## 8.3 Status of completion of the study

The investigator or the subinvestigator will confirm the status of study completion of each subject, and record it in the case report form. If the study has been discontinued, record the date of study discontinuation, reasons for study discontinuation, details about study discontinuation, treatment and course, and follow-up examinations. If the study has been discontinued, follow the procedure in “10.2. Procedures of discontinuation.”

# 9. Measures taken to cope with adverse events and reporting procedures

## 9.1 Securing subjects’ safety

The investigator or the subinvestigator will pay due attention to the safety of subjects, give appropriate treatment to the subjects, and take appropriate measures when any adverse events have occurred.

## 9.2 Follow-up examination

When any adverse events for which causal relationship with the study drug cannot be ruled out are observed at the end of the study, when the clinical study is discontinued due to any safety problems, including the occurrence of adverse events, and when the investigator or the subinvestigator has found it necessary, follow-up examination will be conducted and the results will be recorded until recovery from the symptoms is observed, or until the symptoms become stable and the investigator medically judges that further follow-up is no longer necessary. If a subject failed to show up for follow-up visits for any reasons, such as death, the reason will be recorded.

## 9.3 Reporting of adverse events

The investigator or the subinvestigator will report all adverse events encountered to the sponsor. Immediately report the emergence of any serious adverse events listed below to the head of the study center and the sponsor by telephone or fax irrespective of the causal relationship with the study drug. After that, the investigator will immediately report the events to the head of the study center and the sponsor in writing. When additional information has been requested by the head of the study center and the sponsor, the investigator will provide such information.

[Serious adverse events]

[1] Resulting in death

[2] Life-threatening

[3] Requiring inpatient hospitalization or prolongation of existing hospitalization for treatment

[4] Resulting in persistent or significant disability/incapacity

[5] Leading to a congenital anomaly

[6] Other medically important states

The adverse events listed above include those attributable to adverse reactions to the study drug, or to infections which are suspected to be attributable to the use of the study drug.

[Emergency safety center]

Bellsystem 24, Inc.

[contact] [contact]

Reception hours: Around the clock (24 hours)

## 9.4 Reporting to the regulatory authority

When the sponsor has concluded that any report of serious adverse events received from the investigator falls under the definition of Article 273 of the Enforcement Regulations for the Pharmaceutical Affairs Law, the sponsor will report the adverse events to the regulatory authority according to the provision of the article. Moreover, the adverse events will be reported to the heads and investigators of other study centers.

# 10. Discontinuation criteria and procedures of discontinuation

## 10.1 Discontinuation criteria

When any of the following discontinuation criteria is met, the trial for an individual subject or the entire study will be discontinued pursuant to the “10.2 Procedures of discontinuation.”

(1) Rules regarding discontinuation of the study for individual subjects

When any of the following criteria is met, the trial for the subject concerned will be discontinued.

[1] When the investigator or the subinvestigator has confirmed the recurrence of liver cancer.

[2] When the investigator or the subinvestigator has confirmed the occurrence of a secondary cancer

[3] When the patient died

[4] When the investigator or the subinvestigator has judged that it is difficult to continue the trial

[5] When a violation of “5.2 Inclusion criteria (1),(2),(3),(5)-1)” has been indentified after initiation of administration

[6] When the subject is found to be pregnant

[7] When the subject has withdrawn his or her consent

[8] When the subject failed to show up for follow-up visits due to transfer to another hospital or for other reasons

[9] When the subject took any of the drugs listed in 1 or 2 of “11. Treatment for subjects, (2) Prohibited or caution-required concomitant therapy, (1) Prohibited concomitant drugs and prohibited concomitant food”

[10] Other cases in which the investigator or the subinvestigator has concluded that continuation of the study is difficult

(2) Rules regarding discontinuation of the study

Discontinue the study when any one of the following criteria is met.

[1] When the Institutional Review Board has stated an opinion that continuation of the clinical study is inappropriate.

[2] When the investigator has concluded that it is inappropriate to continue the clinical study

[3] When the study center has violated the Ordinance GCP, study protocol or clinical study contract, and the sponsor has concluded that the violation interferes with the proper conduct of the clinical study

(3) Rules regarding discontinuation of the study for reasons other than those listed above

Discontinue the study when the sponsor has judged that there is no alternative but to discontinue the study for the reasons listed below.

[1] When any events which become a problem in the conduct of the clinical study have been observed in non-clinical studies, and the sponsor has concluded that it is difficult to continue the study

[2] When any important reports regarding safety have been obtained from the clinical study concerned or from other sources of information, and the sponsor has concluded that it is difficult to continue the study

[3] When the sponsor has discontinued the study for any other reasons

## 10.2 Procedures of discontinuation

(1) Procedures for coping with subjects

If the clinical study is discontinued, the investigator or the subinvestigator will immediately discontinue administration of the study drug to the subject concerned, and explain to the subject the fact that the study will be discontinued as well as the reasons of discontinuation. At that time, necessary examinations will be conducted, and the fact that the study is discontinued, the date of discontinuation, reasons of discontinuation, and details (outcome, treatment, etc.) will be recorded.

The subjects who have discontinued the study due to safety problems, such as the occurrence of adverse events, will be followed up to the extent possible, and the details will be recorded.

In the cases of discontinuation of the trial for a subject without involving death or recurrence of HCC, investigate whether or not HCC has recurred in the subject during the period from the start of study drug administration until Week 96 following the start after obtaining an additional consent from the subject.

(2) Reporting of discontinuation by the investigator

When the investigator has decided to discontinue the clinical study, he/she will immediately report that to the sponsor and the head of the study center.

(3) Reporting of discontinuation by the sponsor

The sponsor, after deciding to discontinue the clinical study, will immediately report that to the head of the study center and the investigator.

# 11. Treatment for subjects

Record any treatment other than drug therapy with the study drug given to the subjects, (e.g., a concomitant drug).

(1) Permitted treatment method

Treatments during the study drug administration period

During Step I, to the extent possible, avoid changing the type and dosage regimen of the drug, or discontinuing administration of the drug which the subject has been taking before the start of the study drug administration because gene expression may be affected. If concomitant use of any other drugs has become necessary, long-term administration should be avoided to the extent possible.

In Step II, there are no restrictions regarding the treatments other than those targeted to HCC, unless prohibited concomitant drugs and caution-required concomitant drugs are used.

However, if any other drugs are used during the study drug administration period, the name of the drug used, daily dose, route of administration, administration period and objectives of the use should be recorded.

(2) Prohibited or caution-required treatment methods

Treatments with the following drugs are designated as prohibited or caution-required concomitant treatments because they may interfere with efficacy evaluation of the subjects or assurance of safety. Moreover, concomitant use of both prohibited concomitant drugs and caution-required concomitant drugs is prohibited during the period from the day of the start of study drug administration until Week 8 after the start of administration because gene expression may be affected.

[1] Prohibited concomitant drugs and prohibited concomitant food: Administration and consumption of the following drugs and food are prohibited during the study drug administration period.

|  | Drug classification | Generic name | Brand name |
| --- | --- | --- | --- |
| 1 | Other study drugs |  |  |
| 2 | Anticancer drugs | All anticancer drugs including 5FU, MMC, DXR and tretinoin | |
| 3 | Natural interferons | Interferon α | OIF, Sumiferon |
| Interferon β | IFN β, Feron |
| 4 | Genetically-modified interferons | Peginterferon-α-2a | Pegasys |
| Interferon α-2b | Intron A |
| Peginterferon-α-2b | Pegintron |
| Interferon alfacon-1 | Advaferon |
| Interferon β-1a | Avonex |
| Interferon β-1b | Betaferon |
| 5 | Vitamin K2 | Menatetrenone | Glakay, Kaytwo |
| 6 | Retinoid | Etretinate | Tigason |
| 7 | Vitamin A | Cod-liver oil | Cod-liver oil |
| Retinol palmitate | Chocola A |
| 8 | Antiviral drugs | Ribavirin | Rebetol, Copegus |
| 9 | Supplements containing vitamin A (Lyc-O-Mato Power E, etc.) (health food) | | |
| 10 | Supplements containing vitamin K (health food) | | |

Concomitant administration of the drugs containing the above components will also be prohibited.

[Rationale]

1-5, 10: Because they interfere with or may interfere with evaluation of the efficacy

6: Because they may induce symptoms of adverse reactions resembling those associated with retinoic acid syndrome.

7,9: Because they may induce symptoms of adverse reactions resembling those associated with hypervitaminosis A.

8: Because they are used in the concomitant therapy with interferon.

[2] Caution-required concomitant drugs: The following drugs should be administered with caution during the study drug administration period. The concomitant use of any of these drugs is prohibited from the day of the start of study drug administration until Week 8 after the start of administration.

|  | Drug classification | Generic name | Brand name |
| --- | --- | --- | --- |
| 1 | Ursodesoxycholic acid | Ursodesoxycholic acid | Ubiron, Ursamic, Urso, Urdeston, Urdex, Urdenacin, Gokumisin, Shikichol, Braue, Precoat, Reptor |
| 2 | Phenytoin | Phenytoin-sodium | Aleviatin, Hydantol, Phenytoin |
| 3 | Tetracyclines antibiotics | Tetracycline hydrochloride | Achromycin, Achromycin V |
| Demethylchlortetracycline hydrochloride | Ledermycin |
| Doxycycline hydrochloride | Paldomycin, Vibramycin, Piperamycin, Rasenamycin |
| Minocycline hydrochloride | Minocyclin hydrochloride, Coupelacin, Namimycin, Pardoclin, Minotowa, Minopen, Minomycin |
| 4 | Drugs interfering with glucuronate conjugation | Sodium valproate | Epirenat, Sanoten, Cebotval, Selenica R, Cereb, Depakene, Depakene R, Hyserenin, Baldeken R, Sodium Valproate, Valpram R, Valerin |
| Lorazepam | Azrogen, U-Pan, Rocosgen, Lorazepam, Wypax |

[Rationale]

1: Because the surface-active action of the drug itself may promote absorption of the components, thereby increasing the plasma concentrations

2: Because etretinate (Tigason) has been reported to decrease the protein-binding ability of phenitoin (however, interactions with this component are unknown)

3: Reports of other retinoid have shown that, when used concomitantly with tetracyclines antibiotics, it increased the incidence of headache

4: Because metabolism of this component may be inhibited and the plasma concentration may be increased

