## 7.3 Subject backgrounds

Record the information listed below for the subjects for whom registration confirmation forms have been sent.

[1] Subject number

[2] Before complete cure: As of the time of diagnosis of HCC [the date and procedure of CT examination, diameter of the main tumor, number of tumors, first occurrence/first recurrence (timing of treatment of first occurrence in the case of first recurrence)]

[3] Radical therapy: Date of treatment, operative procedure for treatment (treatment method in the case of topical medical therapy), and the date of CT examination for confirmation of complete cure

[4] Previous history and complications

[5] Results of the tests on registration

[6] Information regarding registration (date of subject registration, date of informed consent, date of birth, gender)

[Flow of registration]

Subjects will be registered according to the following flow.

|  | 8 weeks (56 days) or more and 12 weeks (84 days) or less | 8 weeks (56 days) or less |  |
| --- | --- | --- | --- |

| Subjects |  |  |  |  |  |  |  |  |  |  |  |  |  |  |  |  |  |  |  |  |  |  |  |  |
| --- | --- | --- | --- | --- | --- | --- | --- | --- | --- | --- | --- | --- | --- | --- | --- | --- | --- | --- | --- | --- | --- | --- | --- | --- |
| Hepatocellular carcinoma of first occurrence or first recurrence | |  | Topical medical therapy or surgical resection |  |  |  |  | Briefing to subjects |  | Obtaining subjects’ consent |  |  |  |  |  |  |  |  |  |  |  | Liver biopsy/start of study drug administration |  |
|  |  |  |  |  |  |  |  |  |  |  |  |  |  |  |  |  |  |
|  |  |  |  |  |  |  |  |  |  |  |  |  |  |  |  |  |  |  |  |
| Investigator  or  Subinvestigator |  |  |  |  |  |  |  |  |  |  |  |  |  |  |  |  |  |  |  |  |
| Diagnosis | |  |  | Diagnosis (postoperative confirmation) | |  |  |  | Definite diagnosis | | | |  |  |  | Registration/confirmation of assignment | |  |  |
|  |  |  |  |  |  |  |  |  |  |
|  |  |  |  |  |  |  |  |  |  |  |  |  |  |  |  |  |  |  |  |  |  |  |  |
| Kowa Company, Ltd.  Pharmaceutical Development 2 |  |  |  |  |  |  |  |  |  |  |  |  |  |  |  |  |  |  |  |  |  |  |  |  |
|  |  |  |  |  |  |  |  |  |  |  |  |  |  | Confirmation of eligibility | |  | Subject registration |  | Assignment | |  |  |  |
|  |  |
|  | | | | | | | | | | | | | | | | | | | | | | | | |

[Study schedule]

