| Echocardiography | |  |  |  |  |  |  |  |  |  |  |
| Pulse wave examination | |  |  |  |  |  |  |  |  |  |  |
| Fundus examination | |  |  |  |  |  |  |  |  |  |  |
| Adverse events | |  |  | | | | | | | |  |

: The day before the start of administration and the day of evaluation at Week 8

: Examination will be conducted during the period between the end of radical therapy and the start of study drug administration.

: Examination will be conducted at 48-week intervals.

: Examination will be conducted upon discontinuation of the study if possible.

Note 1: The acceptable range of deviation from the scheduled examination, observation and evaluation during the study period is +28 days for gene expression profile (Week 8) and pharmacokinetics (Week 8); 35 days for abdominal imaging diagnosis, HCV-RNA, HCG tests, tumor markers, fibrosis markers, bone densitometry, endoscopy, ECG, echocardiography，pulse wave examination, and fundus examination; and 7 days for other parameters.

Note 2: Subjects need to be hospitalized on the day of the start of administration and on the day of evaluation at Week 8. Liver biopsy will be performed and blood samples and accumulated urine samples will be collected on the day before the start of administration, with administration of the study drug to start 24 hours after the operation. On the day of evaluation at Week 8, subjects will visit the hospital without taking the study drug, and undergo liver biopsy 4 hours after administration. Blood samples will be collected 4 and 8 hours after administration. Urine samples will be accumulated for 24 hours after administration.

Note 3: Blood pressure parameters will be assessed on the day of the start of administration and at Week 48 and Week 96 of administration. If the systolic blood pressure exceeds 140 mmHg or the diastolic blood pressure exceeds 90 mmHg in two or more consecutive tests, the parameters will be determined on the second or subsequent tests. Determination of creatinine clearance, one of the blood pressure parameters, under increased blood pressure will be conducted to the extent possible. Creatinine clearance will be determined using urine samples collected at home at the timings other than the day of the start of administration (i.e., Week 48 and Week 96 of administration, and examination of blood pressure parameters in the presence of increased blood pressure).

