## 7.4 Gene expression profile

(1) Liver biopsy

Perform liver biopsy to collect liver tissue samples for determinations of the liver gene expression profile drug concentrations.

[1] Liver biopsy procedure

Perform liver biopsy after the absence of the risk of haemorrhage has been confirmed in advance by the blood coagulation test, etc. Under local anesthesia, needle biopsy is performed with the aid of ultrasonography using a Bard Monopty automatic biopsy needle (Max Core). The specification is as follows: depth of insertion; 22 mm, external diameter; 16 G, needle length; 160 mm. The upper limit for the amount of liver tissue samples to be collected per day for determination of the gene expression profile and drug concentrations in the liver will be 20 mg, respectively. The patients will remain at rest for a while after liver biopsy. They will be hospitalized on the days of examination.

[2] Timing of liver biopsy and the acceptable range

On the day before the start of study drug administration and on the day of evaluation at Week 8 after the start of administration (4 hours after administration)

- 4 hours after administration: ±30 minutes

If a deviation from the designated timing of sample collection is within the acceptable range, the sample will be deemed as collected at the designated timing.

If the investigator or the subinvestigator deems that liver biopsy cannot be performed on the designated day of evaluation at Week 8 due to the subject’s health condition, the liver biopsy can be postponed by up to 28 days. In such cases, the period of Step I [the period of administration of two doses, i.e., 300 mg/day (twice daily) and 600 mg/day (twice daily)] will be extended until completion of liver biopsy.

[Rationale for timing of liver biopsy]

The rationale for the timing of liver biopsy is described, as the rationale for selection of the administration period for determination of the gene expression profile, in the section of “Rationale” under “4.4.(3) Study drug administration period” for determination of the gene expression profile.

From the results of the phase I single administration study, the appropriate timing of liver biopsy on the day of evaluation at Week 8 of study drug administration was deemed to be 4 hours after administration, which is close to the time point of the Cmax of unchanged NIK-333.

(2) Determination of the gene expression profile in the liver

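### The Step I ban on caution-required drugs starts one day after the baseline biopsy, so an existing user who complies may be profiled on the drug at baseline and off it at Week 8

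*Protocol*

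**What the plan says.** Section 11(2) states the ban twice. The introductory paragraph covers both the prohibited and the caution-required drugs, gives a possible effect on gene expression as the reason, and sets the period as "prohibited during the period from the day of the start of study drug administration until Week 8 after the start of administration". The entry that introduces the caution-required list repeats it: "The concomitant use of any of these drugs is prohibited from the day of the start of study drug administration until Week 8".

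The baseline samples come earlier. Note 2 to the study schedule in Section 7.3 reads "Liver biopsy will be performed and blood samples and accumulated urine samples will be collected on the day before the start of administration", with dosing to begin 24 hours after the biopsy. Section 7.4(1) gives the two biopsy times as "On the day before the start of study drug administration and on the day of evaluation at Week 8", and Section 7.4(3) uses the same two days for the peripheral blood profile.

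For drugs in general, Section 11(1) asks sites as follows: "During Step I, to the extent possible, avoid changing the type and dosage regimen of the drug, or discontinuing administration of the drug". It applies this to drugs already in use at entry and gives the same gene-expression reason.

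Sections 4.4(2) and 7.4(1) allow the Week 8 biopsy to be put back by up to 28 days and extend Step I until it is done. Section 12.2 compares expression before and after treatment, by dose and by patient. Section 12.7 takes the primary gene-expression result from the Per Protocol Set.

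**The concern.** The ban is meant to keep these drugs from disturbing the expression profiles. A before/after comparison is protected only if co-medication is the same at both samplings. As dated, the ban protects the second profile and leaves the first open.

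The eligibility rules do not close the gap. In Section 5.3, criterion [4] covers other study drugs, anticancer drugs, interferons and vitamin K2. Criterion [7] concerns coagulation and fitness for biopsy, and [14] is left to the investigator's judgement. None names the caution-required drugs.

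Both arms receive NIK-333, so no untreated group shows what stopping one of these drugs does alone. In a subject who stops one and starts NIK-333 within about a day, the two effects cannot be separated. Section 12.2 looks at results patient by patient, where one such subject counts in full. A user who stops on the day of first dose has complied, so this rule does not remove that subject from the primary set. A user kept stable on the drug, with matching co-medication at both biopsies, would be a concomitant-drug violation under Section 12.7 and might be removed.

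**Working it through.** The protocol gives no figure to reproduce here. The check is a comparison of dates, followed by simple arithmetic on what one affected subject would contribute.

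**Start date.** Take the day of first dose as Day 0.
- Baseline biopsy and blood: Day −1 (Sections 7.3 and 7.4).
- Ban starts: Day 0 (Section 11(2), both statements).
- Gap: 0 − (−1) = 1 day during which use is allowed and the baseline is sampled.

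**End date.**
- Week 8 is Day 56, where both statements of the ban end.
- Latest permitted biopsy: 56 + 28 = Day 84.
- Possible uncovered interval: 84 − 56 = 28 days, only if the biopsy is postponed.

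**Weight of an affected subject.** Let *d* be the change in a gene's expression caused by stopping the listed drug. No value of *d* is available, and none is assumed. With *k* such subjects in an arm of 6 (Section 12.6):
- By-patient change = NIK-333 effect + *d*, so that subject carries all of *d*.
- Arm mean change = mean NIK-333 effect + (*k*/6) × *d*. For *k* = 1, 2 and 3 the added term is 0.17*d*, 0.33*d* and 0.50*d*.

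**How likely is any affected subject?** The protocol gives no rate of use at entry, so the rate *p* is an assumption. The chance of at least one user among *n* is 1 − (1 − *p*)^*n*.

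| Assumed *p* | At least one in an arm of 6 | At least one in 12 | Expected number in 12 |
|---|---|---|---|
| 0% | 0% | 0% | 0 |
| 10% | 47% | 72% | 1.2 |
| 20% | 74% | 93% | 2.4 |
| 30% | 88% | 99% | 3.6 |
| 50% | 98% | about 100% | 6.0 |

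These are chances of a user at entry. They become chances of an affected subject only if each user is enrolled and continues up to the biopsy. Section 2.3(2) reports ursodeoxycholic acid use in phase I, also in treated HCC patients, on a dosing day when it was prohibited. That shows use is possible, but not how common it is at entry to this trial.

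**Room for a washout.** Inclusion criterion [4] allows at most 56 days from the complete-cure CT to first dose, so at most 56 − 1 = 55 days to the baseline biopsy. With 14 days as an illustration, up to 55 − 14 = 41 days would remain. Section 7.1 places consent before that CT, so stopping can be agreed in time.

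**The case against.** **The rule permits use up to first dose; it does not require it.** A subject who stops earlier also complies, and the investigator may exclude a user under criterion [14]. This stands. A reader might infer that following the protocol forces an on/off pair of profiles. The text supports only that it may produce one.

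**The drug-by-drug reasons in Section 11(2) concern interaction.** They cite raised NIK-333 levels, protein binding, and headache with retinoids. Those reasons need both drugs present, so a first-dose start suits them. But the same section gives gene expression as the reason for the stricter Step I rule, and the start date does not serve that purpose. It is fair to add that the protocol nowhere shows that stopping one of these drugs changes the profile.

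**Sections 11(1) and 11(2) might be read as contradictory.** That goes too far. The advice in 11(1) is qualified and general, while 11(2) is specific and absolute and would ordinarily prevail. The forced change remains if it does.

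**The end date is partly covered.** Section 11(1) applies throughout Step I, including an extension, and Section 7.8 accepts a biopsy up to 28 days late as the Week 8 evaluation. But 11(1) applies only as far as possible, so it does not replace the ban.

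**A reader might infer that a drug stopped just before first dose would go unrecorded.** The itemised rule in 11(1) does cover only later use ("if any other drugs are used during the study drug administration period, the name of the drug used, daily dose, route of administration"), and the background items in 7.3 list no current drugs. However, Section 11 opens by asking for any other treatment to be recorded, and the case report forms are not shown. The inference cannot be established.

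**The sponsor can handle problem cases, and randomisation protects the dose contrast.** Section 12.7 allows case-by-case decisions with medical experts, but this is discretionary. The 300 mg versus 600 mg comparison is not biased in expectation; the within-arm and by-patient changes are what is exposed.

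**Conclusion.** The concern holds as a minor, conditional timing gap. The ban opens 1 day after the samples it should protect and may close up to 28 days before the second set. An existing user who complies may therefore contribute a change that mixes withdrawal of the listed drug with the effect of NIK-333.

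This depends on at least one user being enrolled and continuing up to the biopsy, and on withdrawal having some effect on expression. The protocol settles neither, and the number affected may be zero. One such subject would be 1 of 6 in an arm (17%) and 1 of 12 overall (8%).

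The documents do not support reading this as a flaw in the whole gene-expression analysis. The study is exploratory, no size of effect is shown, and subjects not taking these drugs are untouched. The change is still worth making because it lets a stated rule serve its own stated purpose at little cost.

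**What to change.** Make the same change in both statements of the ban in Section 11(2):

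1. **Start.** Begin the ban before the baseline biopsy, by a washout that the clinical team sets for each drug. Fourteen days can stand as a placeholder only. It borrows the two-week minimum in Section 4.4(3), which rests on NIK-333 reaching steady state and says nothing about clearance of the listed drugs. Do not enrol subjects who cannot safely stop.
2. **End.** Close the ban when the actual Step I biopsy and its associated blood and urine samples are complete, so that it still applies if the biopsy is postponed.

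Two additions are editorial and optional: a sentence saying that the ban takes precedence over Section 11(1) for the listed drugs, and an item in Section 7.3 recording use of these drugs between consent and first dose.

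**Cost.** The wording change is a few words in two places. Existing users, who must stop by first dose in any case, would stop somewhat earlier. A subject who cannot stop safely would be lost, which matters in a 12-subject study sized on feasibility. The 41 days left after a 14-day washout is a maximum, and eligibility checks, registration and assignment must also fit into the interval before the biopsy.
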